# Effect evaluation of outpatient long-term video EEGs for people with seizure disorders – study protocol of the ALVEEG project: a randomized controlled trial in Germany

**DOI:** 10.1186/s12913-024-11076-y

**Published:** 2024-08-27

**Keywords:** Seizure disorders, Epilepsy, Healthcare management, Outpatient long-term video EEGs, Statutory health insurance, Randomized controlled trial, Equivalence trial

## Abstract

**Background:**

Epilepsy and other seizure disorders account for a high disease burden in Germany. As a timely diagnosis and accurate treatment are crucial, improving the management of these disorders is important. Outside of Germany, outpatient long-term video EEGs (ALVEEGs) have demonstrated the potential to support the diagnosis and management of epilepsy and other seizure disorders. This study aims to evaluate the implementation of ALVEEGs as a new diagnostic pathway in eastern parts of Germany to diagnose epilepsy and other seizure disorders and to assess if ALVEEGs are equally effective as the current inpatient-monitoring gold standard, which is currently only available at a limited number of specialized centers in Germany.

**Methods:**

ALVEEG is a prospective, multicenter, randomized controlled equivalence trial, involving five epilepsy centers in the eastern states of Germany. Patients will be randomized into either intervention (IG) or control group (CG), using a permuted block randomization. The sample size targeted is 688 patients, continuously recruited over the trial. The IG will complete an ALVEEG in a home setting, including getting access to a smartphone app to document seizure activity. The CG will receive care as usual, i.e., inpatient long-term video-EEG monitoring. The primary outcome is the proportion of clinical questions being solved in the IG compared to the CG. Secondary outcomes include hospital stays, time until video EEG, time until diagnosis and result discussion, patients’ health status, quality of life and health competence, and number and form of epilepsy-related events and epileptiform activity. Alongside the trial, a process implementation and health economic evaluation will be conducted.

**Discussion:**

The extensive evaluation of this study, including an implementation and health economic evaluation, will provide valuable information for health policy decision-makers to optimize future delivery of neurological care to patients affected by epilepsy and other seizure disorders and on the uptake of ALVEEG into standard care in Germany.

**Trial registration:**

German Clinical Trials Register (DRKS00032220), date registered: December 11, 2023.

**Supplementary Information:**

The online version contains supplementary material available at 10.1186/s12913-024-11076-y.

## Introduction

### Background and rationale

Epilepsy is one of the most common chronic neurological conditions worldwide, imposing a high burden of disease on people affected and on society [1]. In Germany, around 500,000 people are affected by epilepsy [2]. An accurate diagnosis of epilepsy and other seizure disorders, such as psychogenic non-epileptic seizures or syncopes, is crucial to avoid misdiagnoses and to create a correct treatment plan, leading to an improved quality of life (QoL) for people affected and preventing fatal seizures [3].

Therefore, equipping healthcare systems with the right tools to make a timely diagnosis is important to avoid a lack of healthcare services, especially in rural areas [4]. The current gold standard for diagnosing epilepsy and other seizure disorders is an inpatient long-term video-electroencephalogram (EEG) monitoring (VEM). However, inpatient monitoring is only available at limited specialized centers and is associated with significant time and work resources [5]. Further, there are still fewer neurologists and pediatric neurologists in the rural eastern parts of Germany, reflected by a higher number of epilepsy patients per neurologist, leading to a significant waiting time for inpatient long-term video EEGs [6]. To address these challenges, outpatient long-term video EEGs (ALVEEGs) have already been established in other countries [7]. The development of a new portable sensor technology, enhanced by innovative automated data analyses supported by artificial intelligence (AI), allows ALVEEGs in the patient’s home environment. This advancement facilitates faster and more accurate diagnoses in this setting. By aligning with the treatment gold standard of care, it helps preventing misdiagnoses and inappropriate treatment plans, thereby improving QoL of people affected by epilepsy and other seizure disorders [8].

As shown in a single-center feasibility study in Germany, ALVEEGs were well accepted by patients and clinicians. They may offer an equivalent way of diagnosing epilepsy and other seizure disorders in Germany [8].

The here presented study, funded by the German Innovations Fund of the Federal Joint Committee (G-BA), aims to evaluate if ALVEEGs in an outpatient setting as diagnostic pathways are equally effective as the current inpatient gold standard of VEM to diagnose epilepsy and other seizure disorders. If successful, barriers in diagnosis and treatment care may be resolved, and patients in Germany affected by these disorders may have better and more rapid access to adequate diagnostics and subsequent treatment initiation or optimization.

### Study aim and objective

The aim of ALVEEG is to improve and optimize care of patients experiencing epilepsy and other seizure disorders in Germany by translating case and care management into the patient’s home environment by introducing a new standardized way of diagnosing epilepsy and optimizing disease management in the eastern states of Germany. The objectives of the evaluation are to (1) analyze the effects of ALVEEG on patient care compared to the current standard inpatient VEM, assessing patients who have had at least one seizure in the last 12 months or a diagnosis of epilepsy, (2) observe the implementation of project activities, and (3) conduct a health economic evaluation.

## Methods

The presented study protocol follows the SPIRIT reporting standards [9] and is aligned with the reporting guidelines for randomized trials, i.e., CONSORT [10] and the TIDieR checklist [11] for intervention description and replication.

### Trial design

ALVEEG is a prospective, multicenter, randomized controlled trial (RCT) with a project duration of 4 years. The study is designed as an equivalence trial, with a trial duration of 27 months and continuous patient recruitment.

Patients assigned to the control group (CG) receive care as usual, i.e., inpatient VEM, while those randomized to the intervention group (IG) undergo outpatient ALVEEG.

### Study setting and eligibility criteria epilepsy centers

ALVEEG is conducted in cooperation with five epilepsy centers in the eastern states of Germany (Berlin, Brandenburg, Mecklenburg-West Pomerania, and Saxony). Eligible epilepsy centers had to (1) be led by neurologists/neuropediatrics/epileptologists, (2) meet the technical and spatial requirements for conducting long-term inpatient video EEGs, and (3) treat patients who are part of the statutory health system. Epilepsy centers were excluded if they (1) were located outside the catchment area, (2) did not meet the technical and spatial requirements, or (3) did not treat patients who are part of the statutory health system.

The following five epilepsy centers participate in the study: Charité – Universitätsmedizin Berlin, Epilepsy-Center Berlin-Brandenburg; Charité – Universitätsmedizin Berlin, Germany Epilepsy-Center for Children and Adolescents; University Hospital Greifswald; Epilepsy-Center Kleinwachau; and University Hospital Dresden.

Participating statutory health insurances are BARMER, DAK-Gesundheit and Techniker Krankenkasse (TK).

### Eligibility criteria and patient recruitment

To be eligible to participate in ALVEEG, patients have to (1) have had at least one seizure in the last 12 months or a diagnosis of epilepsy, (2) have an indication 1–4 from OPS 1-210, (3) live in a household with access to at least 4G or faster, (4) be part of the German statutory health insurance system, and (5) present themselves at least at one of the participating epilepsy centers. Patients can only be included if they or their legal representative gave written informed consent. Given the open cohort design of the trial, patients will be continuously recruited by the participating epilepsy centers over the trial duration of 27 months.

Patients are excluded if they (1) have an epilepsy surgery indication (indication 5 from OPS 1-210), (2) present themselves with additional psychosocial needs such as consultation on occupational or driving issues, (3) are privately insured, self-paying patients, or (4) if they or their legal representative does not give informed consent.

In patients with an epilepsy surgery indication, ictal events require some acute neuropsychological testing performed by medical technicians. Therefore, these patients are excluded for medical reasons. Further, patients must have had at least one seizure in the last 12 months or an epilepsy diagnosis to use disease-specific questionnaires during the trial, e.g., the Quality Of Life In Epilepsy (QOLIE-10) questionnaire, to get better insights on seizures relevant for the included population.

### Intervention

The IG will complete an ALVEEG at home, comprising a portable EEG- and electrocardiogram (ECG)-recorder and a mobile data station, including a camera and audio recorder. The ambulatory monitoring system is provided by a medical device company that develops, manufactures, and commercializes diagnostic technologies for brain monitoring applications. EEG data will be reviewed using a review and analysis software, which offers computer-assisted reviews of EEGs, supported by AI. Patients will also get access to the smartphone app Helpilepsy [12], a digital diary for the documentation of seizures and related factors throughout the study. Alternatively, patients can also choose to use a paper diary for documentation.

There will be four appointments in the IG at the participating centers. During the first appointment, the EEG and ECG electrodes will be fitted on the patient’s head and chest to measure brain and heart activity and are connected with a portable amplifier. The ALVEEG will take place in the patient’s home environment, recording EEG, ECG, video, and audio data for up to 6 days. Patients will be monitored throughout the study for possible adverse events (AE; e.g., skin irritations or mild rashes) that might occur, given the nature of the intervention. All AE will be recorded to inform future guidelines and use of ALVEEGs. Patients are also asked to document seizures via the app or the paper diary throughout the monitoring. After completing their ALVEEG, patients can either remove the electrodes themselves at home or they are removed in the clinic when patients return all devices at their second appointment. During the third appointment, results of the ALVEEG will be discussed, and the patient’s therapy and treatment plan will be amended accordingly. The patient will also get a medical findings report. The fourth and final appointment will take place three months after completing the VEM for the last follow-up and the final collection of study-related patient-reported outcome measures (PROMs).

### Study outcomes

The outcomes of the study refer to the healthcare system (macro level), the institutional level (meso level) as well as the individual patient (micro level).

The primary outcome of ALVEEG is the proportion of clinical questions being solved in the IG compared to the CG. A clinical question is considered as solved if (1) a specified diagnosis is needed and provided via long-term video EEG, (2) treatment management needs to be defined and is provided via long-term video EEG, or (3) a specified diagnosis is needed, and treatment management needs to be defined according to findings of the long-term video EEG.

Secondary outcomes (see Table 1), include on the macro level: (1) number of hospital stays, (2) length of hospital stays, (3) inability to work (in days), and (4) number of video EEGs; on the meso level: (5) duration of waiting period for a video EEG (in days), (6) duration of waiting period for diagnosis and result discussion, (7) duration of diagnosis identification using AI, and (8) duration of long-term video EEG; and on the micro level: (9) number of diagnosis specifications, definition of treatment management and diagnosis specifications combined with treatment management, (10) number and form of epilepsy-related events and epileptiform activity, (11) QoL related to epilepsy, (12) QoL, (13) health status, (14) health competence, and (15) contentment, acceptance, and AE.

**Table 1 Tab1:** Secondary outcomes, time points, and measurement instruments

Outcome	Timepoint	Measurement Instrument
Number of diagnosis specifications, treatment management, diagnosis specification & treatment management (IC-CG)	tP1	Study data base
Number and type of epilepsy-related events or epileptiform activity (ictal, interictal, only video as quality indicator) *(IC-CG)*	*tD2*	Study data base
Waiting time for video EEG *(IC-CG)*	*t0-tSens*	Study data base
Duration until discussion of diagnosis/results *(IC-CG)*	*t0-tP1*	Study data base
Epilepsy-related quality of life *(IC-CG)*	*t0,tP2*	QOLIE-1 (PROM) via tablet, study data base
Quality of life *(IC-CG)*	*t0,tP2*	EQ-5D-5L (PROM) via tablet, study data base
Health status *(IC-CG)*	*t0,tP2*	EQ-5D-5L VAS (PROM) via tablet, study data base
Health competence/seizure awareness *(IC-CG)*	*t0,tP2*	Subscale PESOS (PROM) via tablet, study data base

*t0 *at baseline*, tD2 *after diagnosis compilation by the neurologist*, tP1 *appointment to discuss medical findings (patient and neurologist)*, tP2 *3-month follow up appointment (patient and neurologist)*, tSens *time point of sensor/electrodes placement

### Participant timeline

Randomization of patients into either the IG or CG will take place in the participating epilepsy centers at baseline (*t0*), after patients have given their informed consent. The treating neurologist will be informed about the patient’s group assignment, and all included patients are asked to complete REDCap (Research Electronic Data Capture) surveys on PROMs (IG and CG: EQ-5D-5L, EQ-5D-5L (VAS), as well as the QOLIE-10 and a subscale of the PESOS questionnaire). All questionnaires will be saved and managed in REDCap electronic data capture tools, hosted at the University of Nebraska Medical Center. REDCap is a secure, web-based application designed to support data capture for research studies [13, 14].

After randomization, patients will receive either inpatient (CG) or outpatient (IG) long-term VEM, with patients in the IG being trained in how to use ALVEEG (*tSens*). They can also call at any time if problems occur during the monitoring at home (*tMon1-tMon2*), and there will be a check-in on the first day of ALVEEG, led by a medical-technical assistant (MTA). Secondary outcome data will be assessed for both IG and CG throughout the study at different assessment time points (see Fig. 1). After the ALVEEG is completed (*tMon2*), patients in the IG will return the equipment to the hospital (*tEA*). The ALVEEG data will be uploaded into the cloud provided by the medical device company and documented in REDCap (*tAP*). The patient’s practitioner will also get access to the monitoring results, which are evaluated by the neurologist for patients in the IG and CG (*tD2*). After the evaluation of the monitoring is completed, the neurologist will discuss the results and care and treatment plan with the patient in both IG and CG (*tP1*). Patients will additionally answer a survey on their acceptance, contentment, and AE during ALVEEG. The follow-up assessment will take place three months after the discussion of medical findings, with patients in both groups answering the PROM questions in REDCap again (*tP2*).

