### Statistical methods: sample size, recruitment and power calculations

The sample size calculation for the presented equivalence trial is based on the primary endpoint. After consultation with the clinical consortium partners, the proportion of resolved clinical cases in the CG is assumed to be 0.8 (80%). We expect to observe an equivalent rate of treatment successes in the IG, whereby (clinical) equivalence is defined within a margin of +/- 15% deviation from the rate in the CG. This corresponds to an equivalence interval of [0.68–0.92] ([68 − 92%]) for the proportion of clinical questions being solved. This margin is based on assumptions made by clinical experts within the consortium and is further supported by the results of international studies on the subject [15].

Based on a significance level of 0.05 and a power of (1-β) = 90%, applying two proportions z-test results in a sample size of 482 participants. Considering an expected dropout rate of about 30%, the sample size of the study amounts to 688 participants. In order to achieve this sample, an average of approximately five patients must be recruited per center and month.

For the secondary endpoints, a power of 0.83 was computed using a two-sided t-test for 550 patients, taking into account the latency period of the routine data from the participating health insurance funds.

According to estimations by the consortium partners and the involved health insurance companies, it is assumed that the aspired sample size can be achieved for all endpoints.

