### Sequence generation and randomization procedure

For ALVEEG, a permuted block randomization with block sizes of either 2 or 4 patients [16] was performed at the patient level prior to the start of the trial by an independent data analyst of the evaluation team. Each participating center was assigned its own randomization list.

Given the nature of the trial design, blinding the treating neurologist is impossible. After the patients or their legal representatives have given informed consent and the neurologist has discussed their further treatment strategy with them, patients will be aware of their group allocation.

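### Baseline PROMs are described after randomization in an open trial, and nothing ensures that patients complete them before learning their allocation

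*Protocol article*

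**What the plan says.** The Participant timeline section opens with the allocation step: "Randomization of patients into either the IG or CG will take place in the participating epilepsy centers at baseline" (t0), once consent has been given. The next sentence says that the treating neurologist is told the "group assignment, and all included patients are asked to complete REDCap (Research Electronic Data Capture) surveys on PROMs", and names the EQ-5D-5L, its VAS, the QOLIE-10 and a PESOS subscale for both arms.

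The section on sequence generation and randomization says that the treating neurologist cannot be blinded. It adds that, after consent and the neurologist's discussion of the further treatment strategy, "patients will be aware of their group allocation". It does not place that moment before or after the t0 questionnaires.

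The same instruments are repeated at tP2: "The follow-up assessment will take place three months after the discussion of medical findings, with patients in both groups answering the PROM questions". Table 1 lists t0 and tP2 for all four PROM outcomes. The health economic section takes QALYs from the EQ-5D-5L. The Discussion concedes that neurologist and analyst are unblinded and expects no major bias from it, but does not mention the baseline self-reports.

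**The concern.** A baseline value serves as a covariate or a reference for change because allocation cannot have influenced it. Here the narrated order is consent, randomization, neurologist informed, PROMs. No sentence requires the questionnaires to be finished before the allocation is made or before the patient hears of it.

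The measures are subjective, and the two arms offer visibly different experiences: up to six days of recording at home, or an inpatient stay. A patient who has just learned which it will be may rate health status, quality of life or seizure awareness differently. The t0 score would then be partly a reaction to allocation.

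At stake are the PROM secondary outcomes and, through the EQ-5D-5L, possibly the cost-utility analysis. A later analysis plan can choose a method that avoids the t0 value, but it cannot restore a clean baseline once the forms have been filled in.

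**Working it through.** **Order of events.** The article fixes three things: randomization is at t0 after consent, the neurologist is informed, and the PROMs are also at t0. It leaves open when the patient is told relative to the questionnaires. The timeline figure is not available in the text at hand. The supported statement is therefore that the sequence permits a baseline taken with knowledge of allocation, not that it prescribes one.

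**Size of the bias.** The article gives no figure for this, so there is nothing of its own to reproduce. The inputs are assumptions:

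- s: shift in the between-arm baseline difference caused by knowing the allocation, in SD units. Assumed 0.10.
- r: correlation between t0 and tP2 scores. Not given; range 0.4 to 0.6 assumed.
- Equal SD at t0 and tP2, a common within-arm slope, and a reaction that affects the t0 answer only.

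Let δ be the true difference (IG minus CG) at tP2 in SD units. Randomization makes the expected baseline difference zero; the reaction makes it s.

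| Analysis | Expected estimate | Bias at s = 0.10 |
|---|---|---|
| tP2 only | δ | 0 |
| Change from t0 | δ − s | −0.10 SD |
| ANCOVA on t0 | δ − r·s | −r × 0.10 SD |

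With equal SDs the ANCOVA slope equals r, so the bias in absolute value is:

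- r = 0.4: 0.4 × 0.10 = 0.04 SD
- r = 0.5: 0.5 × 0.10 = 0.05 SD
- r = 0.6: 0.6 × 0.10 = 0.06 SD

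The bias is proportional to s: halving the shift to 0.05 SD gives 0.05 SD for a change score and 0.02 to 0.03 SD for ANCOVA. The sign depends on the reaction. If home patients rate themselves higher at t0, or inpatients lower, s is positive and a benefit of home monitoring is understated. The opposite reaction overstates it.

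**QALYs.** The article does not say how utilities are combined over time. If the t0 value enters the calculation, a shift in it carries through; if it does not, there is no effect.

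**The case against.** The strongest reply is that disclosure before the questionnaires is not stated. The sentence tells us that the neurologist is informed and joins the PROM request with a plain conjunction. Patient awareness is placed after a discussion whose timing is not given. Sites may already hand out the tablet first. This stands, and it limits the point to a missing safeguard. It does not remove the point, because nothing in the text puts the PROMs before allocation or disclosure. It is also fair to say that the 0.10 SD shift is assumed, and that only secondary outcomes are involved.

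A reader might go further and infer that the PROMs are powered and analysed by plain t-test, that the precision in the baseline goes unused, and that PROM power falls short of a stated figure. The article does not support this:

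- The sentence "a power of 0.83 was computed using a two-sided t-test for 550 patients" covers the secondary endpoints as a group, and the number is set "taking into account the latency period of the routine data from the participating health insurance funds". No PROM-specific power is stated, so none can be missed.
- A t-test power calculation does not fix the analysis. The Statistical methods section names the t-test only as an example for durations in days, allows multivariable techniques, and defers detail to a statistical analysis plan.
- Leaving the baseline correlation out of a power calculation is conservative, not an error.
- That reading also conflicts with the present point: if the baseline is shifted, adjusting for it introduces bias that a follow-up-only comparison avoids.

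**Conclusion.** The point holds as a gap in the order of data collection. As written, the plan allows the subjective t0 PROMs to be answered by patients who already know their arm; it does not establish that they do. Under an assumed 0.10 SD shift that affects t0 only, a change score is off by 0.10 SD and ANCOVA by 0.04 to 0.06 SD (assumed r of 0.4 to 0.6). A tP2-only comparison is unbiased by the shift. The primary outcome, the proportion of clinical questions solved, does not use these scores. The issue is modest in reach, but it is worth correcting because the remedy is cheap and a clean baseline cannot be recovered afterwards.

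**What to change.** Amend the Participant timeline so that the t0 PROMs are completed and locked in REDCap after consent and before randomization, or at the least before the patient is told the allocation. Time-stamp both the form lock and the allocation so that the order can be shown.

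Recruitment began in April 2024, so some patients may have been enrolled under the present sequence. Keep them in the analysis and report the tP2-only comparison of each PROM as a sensitivity analysis. Do not exclude patients whose form post-dates allocation: that could remove the whole early recruitment period or, if the order varied between patients, select on behaviour after randomization.

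The cost is a small change of sequence within one visit and some REDCap form logic. The system is already planned with mandatory fields and plausibility checks. No extra visit, instrument or patient is needed.

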One major strength of the study is its pragmatic nature, allowing to generate real-world evidence on the use of ALVEEGs in clinical care processes as a new diagnostic pathway in epilepsy centers in Germany. Although we do not expect any possible harm for participating patients, we made sure that potentially occurring AE during the trial will be continuously monitored and patients will have access to professional support throughout the trial.

The evaluation of this study will provide valuable information for decision makers to optimize future delivery of neurological care to patients affected by epilepsy and other seizure disorders, and to guide a possible scale-up of ALVEEGs in Germany. Further, conducting an implementation and health economic evaluation alongside this trial will provide essential information for key stakeholders in the German healthcare system.

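### The protocol is inconsistent on whether secondary outcome (15), above all adverse events, is collected in the control group

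*Protocol article*

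**What the plan says.** The Study outcomes section lists the item as a micro-level secondary outcome: "15) contentment, acceptance, and AE". No group is attached to it.

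Two places describe its collection in terms of the home procedure:

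- Participant timeline: "Patients will additionally answer a survey on their acceptance, contentment, and AE during ALVEEG". By its position the survey belongs to the results discussion (tP1). The sentence itself states neither a time point nor a group.
- Intervention, in a sentence that ties AE to what the IG receives: "Patients will be monitored throughout the study for possible adverse events (AE; e.g., skin irritations or mild rashes) that might occur, given the nature of" (cut here for length). Its purpose is given directly afterwards: "All AE will be recorded to inform future guidelines and use of ALVEEGs".

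Two places read more widely:

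- Participant timeline, earlier in the same paragraph: "Secondary outcome data will be assessed for both IG and CG throughout the study at different assessment time points (see Fig. 1".
- Discussion: "potentially occurring AE during the trial will be continuously monitored".

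**The concern.** The trial is meant to inform whether home monitoring should enter standard care beside or instead of an inpatient stay. For that decision an AE rate in the IG means little without the corresponding rate in the CG. The protocol's own examples are skin reactions, and these are plausible in both arms: Table 1 compares the waiting time to sensor or electrode placement between the groups, so both groups wear electrodes. A one-arm rate cannot separate the effect of the home setting from that of long-term EEG recording as such.

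Collecting some AE in both arms would not be enough if the method differs. Home monitoring comes with a first-day check-in and a telephone contact for problems, and no matching contact is described for the CG. Unless the same items are put to both groups, a difference in rates could reflect how events were sought.

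This is not a detail that an analysis plan can settle later. Items never put to control patients cannot be recovered at the analysis stage.

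**Working it through.** The question is mainly textual, so the statements are set against each other first. The arithmetic then shows what a two-arm comparison could deliver.

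**Evidence for IG-only collection**

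1. *Meaning of ALVEEG.* The term also names the trial, as in Trial design: "ALVEEG is a prospective, multicenter, randomized controlled trial (RCT) with a project duration of 4 years". In the Participant timeline, however, it denotes the home procedure, for example "After the ALVEEG is completed (*tMon2*), patients in the IG will return the equipment to the hospital". IG training and the first-day check-in use the term in the same sense.
2. *Neighbouring sentences.* The tP1 sentence just before the survey sentence and the tP2 sentence just after it both name the two groups. The survey sentence does not.
3. *Placement of AE recording.* It stands in the Intervention section, amid the description of the IG's appointments, and its stated purpose concerns the use of ALVEEGs.
4. *Table 1.* Of the seven micro-level outcomes, (9) to (15), items (9) to (14) each have a row marked as a group comparison. Item (15) has no row, and so no time point, instrument or group marker. Several macro- and meso-level outcomes also lack rows, so this supports the reading without proving it.

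**Evidence for collection in both groups**

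5. The general sentence covers secondary outcomes in IG and CG, and item (15) is one of them. It may not reach every listed item, though. Outcome (7), the time to diagnosis using AI, is listed too, while AI-supported review is described only under Intervention.
6. The Intervention section has AE monitoring run throughout the study, and the Discussion has it run during the trial. Neither excludes the CG.

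**Result of the comparison.** Two statements point one way and two the other. No section gives a form, time point or procedure for obtaining item (15) from control patients.

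**Precision if both arms are asked**

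Inputs: control proportion 0.80, margin 0.12 absolute (0.80 to 0.68 or 0.92), significance level 0.05, power 90%, total 482, all from the sample size section. Equal allocation is assumed.

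- The plan's own figure, by two one-sided tests with true difference 0: n per arm = 2 × 0.8 × 0.2 × (1.645 + 1.645)² / 0.12² = 0.32 × 10.82 / 0.0144 ≈ 240.5, rounded up to 241. The total is 482, which matches the protocol.
- Half-width of the 95% confidence interval for a risk difference, same risk p in both arms: 1.96 × √(2p(1 − p)/241).

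| Assumed AE risk | Calculation | Half-width | Expected events per arm |
|---|---|---|---|
| 5% | 1.96 × √(2 × 0.05 × 0.95/241) | 3.9 points | 241 × 0.05 ≈ 12 |
| 2% | 1.96 × √(2 × 0.02 × 0.98/241) | 2.5 points | 241 × 0.02 ≈ 5 |

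The protocol gives no AE risk, so 5% and 2% are assumptions. With about five events per arm the normal approximation is rough.

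**The case against.** A reader might infer that outcome (15) has no control data at all, that control patients are never asked, and that the trial cannot compare the two settings on safety. The documents do not support that. The paragraph with the survey sentence also says that secondary outcome data are assessed in both groups. The survey sentence speaks of patients without restriction and follows directly on one about both groups. ALVEEG is also the trial's name, so the phrase could mean during the trial. AE capture does not rest on the survey alone, and nothing excludes the CG. Fig. 1, to which the reader is referred for the time points, is not available here, and an article commonly leaves survey forms to the full protocol.

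This stands as far as it goes: IG-only collection is the likelier reading of the specific sentences, not an established fact. It does not remove the point. The wider sentences name no way of collecting item (15) in the CG, and the sentence that does describe collection is worded around the home procedure. A site following it could reasonably give the survey to IG patients only.

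Two further objections are fair. First, acceptance of and contentment with a home device can properly be described in the IG alone. The statistical methods section says only that inference focuses in principle on group differences, so not every secondary outcome needs a comparison. The weight therefore lies on AE. Second, the half-widths describe what the remedy would achieve; they do not measure an error in the present text.

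**Conclusion.** The protocol contradicts itself on whether AE, as part of secondary outcome (15), are collected in the CG, and the passages must be reconciled. The consequence is conditional: if the survey sentence is followed as worded, AE are solicited systematically in the IG only, and no IG-CG difference can be estimated from those data. The stronger statement, that control data are certainly absent, goes beyond the text.

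If both arms are asked, the risk difference can be estimated to within about 3.9 points at 5% risk or 2.5 points at 2%. This rests on those assumed risks, equal allocation, and 241 patients per arm with survey data at tP1. The change should be made, because it is cheap and the missing answers cannot be obtained afterwards. Confidence is moderate, since Fig. 1 and the full protocol could show that both arms are already asked. In that case only the wording needs correcting.

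**What to change.** 1. Reword the survey sentence in the Participant timeline, for example: *At tP1, patients in both IG and CG answer the same items on AE and general satisfaction relating to their long-term video EEG; patients in the IG also answer items on the home device.*
2. Align the Intervention section so that AE recording is stated for both groups by the same method, and give outcome (15) a Table 1 row with group, time point and instrument.
3. Report the IG-CG risk difference for AE with a 95% confidence interval, using a method suited to small counts if events are few.
4. Label the home-device items as IG-only and descriptive. If IG-only collection of AE is in fact intended, give AE the same label and make no comparative safety statement from these data.

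Cost: a short amendment and a few extra items for control patients, at a visit they already attend and on the tablet form already in use. Recruitment began in April 2024 and is planned to run to June 2026. Control patients who have already passed tP1 will lack the items, so the comparison should be limited to patients reaching tP1 after the change in both arms, with the resulting number reported. That number would be below 241 per arm if many have already passed tP1, and the interval correspondingly wider.
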